### Diagnostic accuracy study

All patients who consent will be entered into the diagnostic study; patients with a diagnosis of possible TIA or minor stroke will be entered only into the diagnostic study.

The primary care physician will complete the usual local TIA clinic referral form. In addition, the PCP will record the presence or absence of symptoms, signs and past medical history relevant to the diagnosis of TIA, including individual features to enable the ABCD2 score to be calculated: age, blood pressure, clinical features including presence of unilateral weakness and speech impairment, duration of symptoms and diabetes [5]. The PCP will provide a level of certainty of diagnosis based upon clinical judgement: probable or possible.

All patients will then be referred to a specialist clinic as per NICE guidelines (with the degree of urgency dictated by the ABCD2 score) [6]. At the TIA clinic, the diagnosis, ABCD2 score and clinical features will be recorded. Patients will be asked to give consent that their clinical notes can be reviewed to ascertain their final diagnosis (as a final diagnosis may not be reached at the initial specialist appointment).

### Summary of procedures and staffroles

Throughout the trial, the primary care physicians will be instructed to follow usual practice, which should be consistent with the 2008 NICE stroke guidelines [6]. All patients with suspected TIA or minor stroke should be continued on their anti-platelet treatment or started on aspirin 300 mg daily unless there are contraindications and referred to a specialist clinic (with the degree of urgency dictated by the ABCD2 score) [6]. The intervention group will receive treatment additional to this usual care.

#### Initial presentation in daytime general practice

Participating general practices have a lead GP, who coordinates recruitment into the trial. Patients may present with suspected TIA at any time to a GP in the practice, who may be assisted in aspects of patient care by a practice nurse. When a patient presents, the clinician will take a history, examine the patient and come to an initial diagnosis of possible or probable TIA or minor stroke as per usual practice, and then:

1. Inform the patient of the suspected diagnosis as per usual practice.

2. Discuss the information sheet with the patient.

3. Confirm the inclusion and exclusion criteria.

The patient will be given time to consider the information and to ask questions. The clinician will then:

4. Obtain informed consent if the patient is willing to take part.

5. Record clinical features and whether TIA is probable or possible.

For patients diagnosed with probable TIA or minor stroke, the clinician will also undertake the following:

6. Consider the relative indications and contraindications to therapy.

7. Take the patient’s blood pressure.

8. Record any current medication.

9. Randomise the patient to the intervention or control arm.

10. Prescribe and dispense the allocated medication.

11. Ask the patient to bring their medication to the specialist clinic.

Finally, all patients will be referred to the TIA clinic with urgency determined by local guidelines. The GP will also arrange any additional appropriate follow-up consistent with usual practice.

#### Initial presentation in out-of-hours general practice

Out of the hours of 8am to 6.30pm Monday to Friday, GP care is usually provided by GPs who are not from the patient’s weekday general practice. A limited number of out-of-hours general practitioners will be trained to recruit patients into the trial. When a patient presents to a trained out-of-hours GP, the GP will take a history, examine the patient and come to an initial diagnosis of possible or probable TIA or minor stroke as per usual practice, and then:

1. Inform the patient of the suspected diagnosis as per usual practice.

2. Discuss the information sheet with the patient.

3. Confirm the inclusion and exclusion criteria.

The patient will be given time to consider the information and to ask questions. The GP will then:

4. Obtain informed consent if the patient is willing to take part.

5. Record clinical features and whether TIA is probable or possible.

For patients diagnosed with probable TIA or minor stroke, the GP will also undertake the following:

6. Consider the relative indications and contraindications to therapy.

7. Take the patient’s blood pressure.

8. Record any current medication.

9. Randomise the patient to the intervention or control arm.

10. Prescribe and dispense the allocated medication.

11. Ask the patient to bring their medication to the specialist clinic.

Finally, all patients will be referred to the TIA clinic with urgency determined by local guidelines and the daytime general practice informed by the time it reopens. The GP will also arrange any additional appropriate follow-up consistent with usual practice.

#### Initial presentation in the emergency department

Participating emergency departments will have a team of specialist nurses who support recruitment into the trial and recruitment will only occur when a specialist nurse is available. When a patient presents, the emergency department doctor will take a history, examine the patient and come to an initial diagnosis of possible or probable TIA or minor stroke as per usual practice and then:

1. Inform the patient of the suspected diagnosis as per usual practice and contact the specialist nurse.

The specialist nurse will then:

2. Discuss the information sheet with the patient.

3. Confirm the inclusion and exclusion criteria.

The patient will be given time to consider the information and to ask questions. The specialist nurse, supported by the emergency department doctor, will then:

4. Obtain informed consent if the patient is willing to take part.

5. Record clinical features and whether TIA is probable or possible.

For patients diagnosed with probable TIA or minor stroke, the specialist nurse, supported by the emergency department doctor, will also undertake the following:

6. Consider the relative indications and contraindications to therapy.

7. Take the patient’s blood pressure.

8. Record any current medication.

9. Randomise the patient to the intervention or control arm.

10. Prescribe and dispense the allocated medication.

11. Ask the patient to bring their medication to the specialist clinic.

Finally, all patients will be referred to the TIA clinic with urgency determined by local guidelines. The emergency department doctor will also arrange any additional appropriate follow-up consistent with usual practice.

#### Specialist clinic

All patients will have been referred to the TIA clinic as per local protocol consistent with NICE guidelines and therefore will usually be reviewed within 7 days of symptom onset (or within 24 hours for higher risk TIAs). Specialists will manage patients according to their usual practice, including changing any medication started by the primary care physician. In addition, the specialist doctor, supported by nursing staff, willrecord clinical features, ABCD2 score, blood pressure, final diagnosis, current medication, persistence with primary care initiated medication and changes to medication.

Additionally, the research nurse will check the patient’s hospital record for a final diagnosis when this is available if it is not confirmed during the initial TIA clinic attendance; the research nurse will also obtain an up-to-date medication list from the patient’s GP record if this has not been provided at initial presentation.

### Outcome measures

Initial assessments of outcome measures for a future RCT will be made to assess their feasibility. Additional pilot RCT outcome measures will also be recorded specifically to examine recruitment feasibility. The diagnostic accuracy study will compare the primary care physician’s and the specialist’sdiagnoses and risk stratification scores. The same outcomes will be measured for both the pilot RCT and diagnostic studies.

#### Outcome measures for the future randomised control trial

##### Primary outcome measure

The number ofstrokes within 90 days of randomisation.

### Secondary outcome measures

Clinical outcomes within 90 days of randomisation:

• All vascular events

• All major bleeding

• Death

• Ischaemic stroke

• Haemorrhagic stroke

• Fatal stroke

• Disabling stroke

• Non-disabling stroke

• TIA

We will also explore the benefit of analysing clinical outcomes at different lengths of time, including 7 days from randomisation, 7 and 90 days from first symptoms, and between randomisation and the first specialist appointment.

The definition of a TIA is ‘a transient episode of neurological dysfunction caused by focal brain, spinal cord, or retinal ischemia, without acute infarction’, with the absence of infarction supported by appropriate imaging when available [21].

#### Adverse events

Unplanned hospitalisation and falls between entry into the trial and the first specialist appointment will be reported as possible adverse events.GP contacts will be recorded. If Read codes suggest treatment has led to additional GP contacts, the research team will retrospectively analyse the GP record for further details.

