### Trial interventions

#### Intervention plus usual care group

Intervention group patients will be treated with additional secondary prevention medications, unless there are clinical contraindications, prior to referral to a specialist clinic. Treatment will comprise of dual anti-platelets, blood-pressure lowering medication, and simvastatin 40 mg. All patients will then be referred to a specialist clinic as per NICE guidelines (with the degree of urgency dictated by the ABCD2 score) [6].

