### Follow-up

There will be a 90-day follow-up clinic at the hospital. This will be supplemented by a review of GP and hospital records, flagging with the NHS Central Register and telephone contact or home visits for patients who do not or cannot attend the 90-day follow-up clinic. These follow-up mechanisms will:

• Confirm the final diagnosis.

• Record the patient’s blood pressure and serum cholesterol at 90 days.

• Identify primary and secondary outcomes.

• Monitor for serious adverse events and deaths.

• Record any changes in treatment and persistence with medication at 90 days.

• Collate cost data.

• Assess the patient’s quality of life at 90 days.

• Record side effects.

Prior to contacting participants for a follow-up, their health status will be established via their GPs to establish that they are not deceased and to ascertain whether their mental capacity has been lost. Participants identified as having lost capacity will be contacted and an appropriate consultee appointed. Detailed information about the trial will be provided to the consultee, and if in agreement an appointment will be made for the participant’s follow-up visit, at which the consultee must be present and must sign a declaration form to confirm their accordance.

Blood pressure and serum cholesterol readings taken at the 90-day follow-up clinic will be sent to the patients’ GP.

Where strokes are identified, anonymised copies of the relevant clinical information (from GP and hospital records, post-mortem reports, scan reports and so on) will be obtained and sent to an independent end-point committee, who will be blinded to treatment allocation. Independently of each other, the end-point committee will determine whether or not a stroke occurred, and if so, what sort of a stroke it was. Characterisation will include: ischaemic or haemorrhagic and disabling, non-disabling or TIA. Secondary outcomes will also include all vascular events, all major bleeding and deaths. Relevant clinical records will be scrutinised by an independent expert blinded to treatment allocation, who will determine whether or not a vascular event or major bleeding occurred, and what it was using standard case definitions. All hospital admissions will be scrutinised for possible adverse events and the clinical records sent to an independent expert for review.

We will follow up all patients, including those in the RCT and the diagnostic study.

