There is currently no evidence that rapid administration of statin treatment is beneficial. The FASTER study investigated treatment with simvastatin 40 mg once daily versus a placebo in 392 patients within 24 hours of a stroke or TIA and failed to demonstrate whether this was either harmful or beneficial (the absolute risk increase of stroke within 90 days was 3.3%; the 95% confidence interval was −2.3% to 8.9%; *P*=0.25) [12]. However, there is evidence that statin treatment reduces the incidence of recurrent stroke in the long term in people who have experienced a stroke or TIA [28-30] and statin treatment is recommended for all patients who experience ischaemic stroke/TIA [6].

Approximately 50% of people referred to TIA clinics have not experienced a TIA or minor stroke [31]. Common alternate diagnoses include migraine, faints, vertigo and epilepsy [32]. It is therefore likely that this trial will increase the number of people who are given blood pressure treatment, statin therapy and anti-platelet agents for the brief period (usually less than 7 days) before they are reviewed by the specialist clinic. However, all these agents are commonly used in primary care to prevent cardiovascular disease, and it is unlikely that 1 to 7 days of unnecessary treatment will cause substantial harm – indeed, since clinicians use cardiovascular risk factors to assess the likelihood of TIA or minor stroke, many patients with alternative diagnoses may benefit from these drugs and the focus on their cardiovascular risk that a suspected diagnosis brings. Significant adverse events that occur prior to specialist clinic attendance will, however, be recorded.

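### Falls and unplanned hospitalisations are reported only up to the first specialist appointment: a variable window that disagrees with the follow-up section on admissions and leaves later falls without a defined count

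*Protocol article*

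**What the plan says.** The protocol's Adverse events section sets the reporting window: "Unplanned hospitalisation and falls between entry into the trial and the first specialist appointment will be reported as possible adverse events". The window therefore ends at the clinic visit. On its timing, the Specialist clinic section says patients "will usually be reviewed within 7 days of symptom onset (or within 24 hours for higher risk TIAs").

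The Follow-up section, which describes the 90-day follow-up, is wider for admissions: "All hospital admissions will be scrutinised for possible adverse events and the clinical records sent to an independent expert for review". It also provides for monitoring of serious adverse events and deaths and for recording side effects. The Cost data section collects hospital admissions over 90 days. The Discussion adds, on short unnecessary treatment before the clinic: "Significant adverse events that occur prior to specialist clinic attendance will, however, be recorded".

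In the daytime general practice procedure the order is "Randomise the patient to the intervention or control arm", then "Prescribe and dispense the allocated medication", and after the numbered steps "Finally, all patients will be referred to the TIA clinic with urgency determined by local guidelines". The out-of-hours and emergency department procedures follow the same order. The Secondary outcome measures section, by contrast, counts clinical events, including major bleeding and death, over a fixed 90 days from randomisation. There, 7 days and the interval up to the specialist visit are further periods to explore.

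**The concern.** A harm count needs the same observation time in each arm, or an analysis that allows for unequal time. Here observation stops at an event that follows randomisation. The protocol describes no placebo. The clinician prescribes the allocated drugs, and blinding is mentioned only for those who adjudicate outcomes. Whoever arranges the referral therefore knows the arm, and the wait could come to differ between arms for reasons unrelated to harm.

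The window is also short. The intervention adds or increases blood-pressure treatment, for which falls are a foreseeable harm. Those drugs may continue after the clinic visit, and the Process of care measures section records persistence with treatment at 90 days. A fall in week three that leads to no admission is not counted under any stated definition.

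Aim 4 asks whether there were any adverse events and sets no time limit. The Adverse events section stands ahead of the heading for additional pilot outcomes, among measures intended for the future trial, and aim 3 asks whether those measures are feasible. A weak definition here could pass into the main trial.

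**Working it through.** The protocol gives no event rate, power or sample size for falls or hospitalisation, so there is no stated figure to reproduce. The check has three parts.

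**1. Share of follow-up covered.** Inputs: windows of about 1 and 7 days (Specialist clinic section) and follow-up of 90 days. The clinic targets run from symptom onset and hold only usually, so the window from trial entry may be shorter or longer.
- 1/90 = 1.1%
- 7/90 = 7.8%

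About 92% to 99% of follow-up time lies outside the window.

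**2. Effect of unequal waits at equal risk.** With daily rate r in both arms and window w days, the risk is 1 − exp(−r·w). The rates and waits below are assumptions.
- Equal waits: risk ratio 1.00 at any r.
- 4 v 5 days, r = 0.005: (1 − exp(−0.020)) / (1 − exp(−0.025)) = 1.98% / 2.47% = 0.80.
- 3 v 4 days, r = 0.005: 1.49% / 1.98% = 0.75.
- With r = 0.001 or 0.002 the ratios are unchanged to two decimals.

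At low rates the ratio is close to the ratio of the waits. It therefore shows the mechanism and does not estimate any actual bias.

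**3. Expected patients with a fall per arm.** Inputs: 100 trial patients (Recruitment section), assumed 50 per arm. Formula: 50 × (1 − exp(−r·w)).

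| Assumed r per day | 4-day window | 90-day window |
|---|---|---|
| 0.001 | 0.20 | 4.3 |
| 0.002 | 0.40 | 8.2 |
| 0.005 | 0.99 | 18.1 |

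On these assumptions the pre-clinic window yields about one patient per arm at most.

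**Coverage, section by section.**

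| Harm | Adverse events section | Elsewhere |
|---|---|---|
| Unplanned hospitalisation | To first specialist appointment | All admissions reviewed (Follow-up); 90-day admissions (Cost data) |
| Fall with admission | To first specialist appointment | Reached through review of admissions |
| Fall without admission | To first specialist appointment | Not named; could surface only through serious adverse event monitoring, GP contacts or the 90-day side-effect questionnaire |
| Major bleeding, death | Not mentioned | Fixed 90 days (Secondary outcome measures) |

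**The case against.** The strongest defence is that the pre-clinic interval is the treatment period of interest. Afterwards, specialists manage both arms by usual practice and may change what the primary care physician started, so the contrast between arms is clearest before the visit. This stands, and it is a good reason to keep the pre-clinic count. It is not a reason to have no fixed-window count beside it.

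Referral urgency is also tied to a baseline score, "with the degree of urgency dictated by the ABCD2 score", and that score is a minimisation factor. This makes equal waits plausible. It balances the score, however, and cannot prevent differences in referral that arise after allocation.

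The pilot is small and descriptive: the Analysis section reserves regression for the main trial. At 50 per arm and r = 0.005, waits of 4 and 5 days mean about 1.0 and 1.2 patients, which nobody could tell apart. This also stands, and it limits the consequence for the pilot itself.

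Four stronger readings are tempting but unsupported:
- A reader might infer that later hospitalisations go uncounted. The Follow-up and Cost data sections show otherwise.
- A reader might take the Discussion sentence to exclude later harms. It says early events will be recorded and does not say later ones will not be.
- A reader might infer that all later falls are lost. Those leading to admission are within the review of admissions, and others may surface indirectly.
- A reader might treat the lack of a rule for patients who never attend as an error. A condensed article may leave that to the full protocol or analysis plan.

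**Conclusion.** The point holds in a limited form. The stated window for falls and unplanned hospitalisation varies between patients and closes at a post-randomisation event arranged without blinding. Counts can therefore differ by arm if waits differ. It would go too far to conclude that the comparison of harms is distorted: the protocol gives no waits by arm, neither size nor direction can be determined, and equal waits give no distortion. The ratios of 0.75 and 0.80 rest wholly on assumed waits.

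Two faults come from the text itself. The Adverse events and Follow-up sections give different windows for admissions, and falls without admission after the clinic visit have no defined count. The window covers about 1% to 8% of follow-up if the clinic targets are met. The expected fall counts also rest on assumed daily rates of 0.1% to 0.5% and equal arms of 50. This is a worthwhile, inexpensive improvement to the definition of harms and does not threaten the trial's main purpose.

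**What to change.** Report falls and unplanned hospitalisations by arm at 7 and 90 days from randomisation, for all randomised patients. Both time points already appear in the Secondary outcome measures section. Use the GP and hospital record review and the 90-day contact already planned. Keep the count up to the first specialist appointment as a descriptive addition, and show waiting time by arm beside it. Align the Adverse events section with the Follow-up section so that one statement says which admissions are reported as adverse events and over what period.

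The cost is mainly wording and some extraction from records. There are two drawbacks. Counts at 90 days include events on treatment chosen by the specialist, which is why the 7-day and pre-clinic counts should stand beside them. Recruitment closed on 31 December 2012 (Trial status section), so a new falls question may come too late for pilot patients. Pilot falls may then have to come from record review, which may miss falls that were never reported to a clinician. A direct falls question can be carried into the main trial.

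### The detailed GP-record review for harms is triggered by a judgement that treatment caused the contact, so non-serious harms found through this one source may be ascertained unequally between arms

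*Protocol article*

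**What the plan says.** The Adverse events section of the protocol article has three elements.

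- Two events are reported outright: "Unplanned hospitalisation and falls between entry into the trial and the first specialist appointment will be reported as possible adverse events".
- Contacts are collected without condition: "GP contacts will be recorded".
- A closer look is conditional: "If Read codes suggest treatment has led to additional GP contacts, the research team will retrospectively analyse the GP record for further details".

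The Follow-up section sets out a separate route. It provides a 90-day hospital clinic and says: "This will be supplemented by a review of GP and hospital records". Its listed purposes include "Monitor for serious adverse events and deaths" and recording side effects. On admissions it says: "All hospital admissions will be scrutinised for possible adverse events and the clinical records sent to an independent expert for review". For vascular events and major bleeding it says: "Relevant clinical records will be scrutinised by an independent expert blinded to treatment allocation". It closes with "We will follow up all patients, including those in the RCT and the diagnostic study".

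A standard side-effect questionnaire at 90 days is mentioned under Sample size calculation, within the additional pilot outcome measures.

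**The concern.** The conditional step asks someone to decide that treatment caused a contact before the record that would inform the decision has been opened. In a trial of extra drugs against no extra drugs, such a decision is not neutral between arms. A code for dizziness, headache or stomach upset is readily put down to a newly started drug. The same code in a patient who was given nothing additional is less likely to be, and that record stays closed.

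Whether there were any adverse events is one of the five questions in the Aims. The Discussion argues that a few days of unnecessary treatment are unlikely to cause substantial harm, while noting that about half of TIA-clinic referrals prove not to be TIA or minor stroke. Minor complaints taken to the GP are part of the evidence on that argument. If they are looked for harder in one arm, this source may overstate harm there. If the codes are too non-specific to suggest a drug effect, it may understate it.

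**Working it through.** The plan states no figure on this point, so there is nothing to reproduce. The check sets the relevant sections side by side.

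**1. What opens the record.** Under Adverse events, recording contacts is unconditional. The detailed analysis depends on Read codes suggesting that treatment led to additional contacts. The criterion therefore refers to treatment, not to the type or number of contacts alone.

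**2. Who has treatment to which a contact can be attributed.** Under Randomisation, patients are assigned to additional treatment plus usual care or to usual care only. Under Trial interventions, the intervention arm may receive dipyridamole, a blood-pressure drug and simvastatin on top of aspirin. Under Usual care group, controls start aspirin if not already on anti-platelet therapy. No placebo is described. Both arms can have a newly started drug, but the intervention arm can have several more.

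**3. Who judges.** The step is assigned to the research team. Their blinding status is not stated. Under Follow-up, blinding is stated for the end-point committee and for the expert on vascular events and major bleeding.

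**4. Which harms depend on this step.**

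| Source | Conditional on attribution to treatment? |
|---|---|
| Unplanned hospitalisation, falls (to first specialist appointment) | No |
| Counts of GP contacts | No |
| Serious adverse events, deaths | No |
| All hospital admissions, sent to an independent expert | No |
| Vascular events, major bleeding (blinded expert) | No |
| Side-effect questionnaire at 90 days | No |
| General review of GP and hospital records at follow-up | No |
| Detailed analysis of the GP record for contacts | **Yes** |

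Only the last row is exposed.

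**5. Direction, with assumed figures.** Suppose equal arms of 50 (100 / 2) and a complaint of this kind in 15% of patients in each arm, so there is no true difference: 0.15 × 50 = 7.5 per arm.

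- All intervention cases and none to a quarter of control cases trigger a look-up: 7.5 records opened against 0 to 0.25 × 7.5 = 1.9.
- Only half of the intervention cases trigger: 0.5 × 7.5 = 3.75 against the same 0 to 1.9.
- The same criterion in both arms: 7.5 against 7.5.

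The 15%, the trigger proportions and the equal split are all assumptions without a source in the article. They count records opened, not adverse events reported. They show which way the mechanism runs and do not estimate its size.

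**The case against.** The strongest reply is that the conditional step is a minor supplement to a broad collection of harms. Much of that stands. A reader might infer three stronger things from the sentence, and the article supports none of them.

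- *That GP records are examined for harms only when the trigger is met.* Follow-up provides a review of GP and hospital records for all patients, and Read codes play no part in it.
- *That harms as a whole are sought in one arm and cannot be compared.* Most sources carry no restriction by arm, and the side-effect questionnaire may well cover the same minor complaints.
- *That an unblinded team makes the judgement.* The article is silent on the team's blinding. Silence supports saying that none is stated, and no more.

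Two points of reading also count against overstatement. Aspirin started in a control could count as treatment, so the trigger is not formally limited to one arm. The word additional may imply a comparison of groups, where an excess of contacts prompts a closer look, and not a patient-by-patient decision. The sentence does not settle this. The group reading does not remove the difficulty, because nothing says that both arms' records would then be opened.

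It is also fair that a code list and the masking of extracts could sit in the full protocol. Their absence from an article is no fault. The criticism rests on the rule the article does state, which makes review depend on attribution to treatment.

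The other sources do not wholly replace this one. Admissions and serious events miss complaints managed by the GP. A questionnaire at 90 days is a weak record of the period before the clinic, which the Discussion puts at usually less than 7 days. The general review at follow-up may reach the same contacts, but if it already examined each one in detail, the conditional step would be unnecessary.

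**Conclusion.** The concern holds for one source of harm data. Followed as written, the rule for detailed GP-record review will tend to open more records in the intervention arm, so the non-serious harms it finds are open to differential ascertainment. This assumes that attribution to treatment is more likely where more drugs have been started, which is reasonable in a comparison without a described placebo but is not demonstrated by any figure in the article.

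The size cannot be derived. The consequence is limited: the article states no decision rule for the main trial that turns on comparing minor primary-care complaints between arms, so it does not support saying that the decision to proceed would be misinformed. This is a worthwhile and inexpensive improvement to one rule, and the rest of the harm collection is left intact.

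**What to change.** Replace the causal condition with one criterion applied identically to both arms:

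1. Take all GP contacts of every randomised patient over one fixed period from randomisation.
2. Screen them against a set of Read codes listed in advance.
3. Examine the record for every match, whatever the allocation, and report the findings by arm.
4. Where practical, remove allocation and drug names from the extracts and have the existing independent expert classify them.

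Any judgement about cause then comes after ascertainment and no longer controls it. It would also help to say how this step relates to the general record review under Follow-up.

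The cost is a code list, a change of wording and modest extra review for about 100 randomised patients. Their GP contacts are already recorded, and GP contacts are also among the 90-day cost data. A narrow list would miss effects coded as something else, but by the same rule in both arms. The change does not remove differences in consulting or coding that arise because the treating doctor, who prescribes the allocated drugs, knows the allocation.
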